**Fig. 2 Fig2:**
[figure not shown]
Content for the schedule of enrolment, interventions, and assessments

### Study endpoints

The primary endpoint will be the percentage incidence of anastomotic leakage after TLRG. We will determine whether or not EOF at POD1 is non-inferior in terms of the occurrence of post-operative fistulas, including anastomotic leakage. Anastomotic leakage will be defined as the breakdown of the connection and subsequent leakage of digestive system fluid from a surgical anastomosis of digestive system structures. If anastomotic leakage is clinically suspected post-operatively, digestive tract radiography will be performed to diagnose the leak. Usually, sufficient abdominal drainage is the most effective treatment.

The secondary endpoints are post-operative recovery and nutritional status, as follows: (1) post-operative complications (n) at 30 days according to the Clavien Dindo classification, which include incisional infection, abdominal abscess, intraperitoneal hemorrhage, anastomotic bleeding, postoperative intestinal obstruction, pancreatitis, pulmonary complications, and others organ complications; (2) the time of first flatus and defecation (day); (3) post-operative length of stay (day); and (4) hospitalization costs (Yuan).

### Sample size estimate

Based on the data from the CLASS-01 study [21], the anastomotic leakage rate in this trial is defined as 1.9%, and previous RCTs involving open gastrectomy concluded that there were no significant differences between EOF and traditional oral feeding (DOF) with regard to the risk for anastomotic leakage [19, 24]. To verify that EOF is non-inferior regarding the anastomotic leakage rate after laparoscopic radical gastrectomy, we designed a non-inferiority test with a non-inferiority margin of 5% (α = 0.05, β = 0.20, and a power of 80%). Considering both clinical and statistical considerations like intolerance of enteral nutritions, therefore, no less than 160 participants (80 participants in each group) will be required. Allowing for a 20% drop-out and withdrawals before trial completion, we decided to recruit a total of 200 participants (100 participants in each group) [21].

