### Statistical analysis

The intention-to-treat principle will be applied in all analyses with an assumed drop-out rate. Normally distributed continuous variables will be described as the mean with corresponding SDs, and non-normally distributed or categorical variables will be described as medians with the corresponding range or percentages and frequencies. Normally or non-normally distributed continuous data will be compared by Student’s *t*-test or the Mann–Whitney U test, and the chi-square test and Fisher’s exact test will be used to compare categorical variables, as indicated. With the exception of the primary outcome, secondary outcomes, such as post-operative complications, time of first flatus and defecation, and post-operative length of stay, will also be compared. The potential risk factors for intolerance of EOF and post-operative complications will be identified using a multivariate analysis. A blinded statistician will analyze all of the data using a two-sided *P* value < 0.05 to represent statistical significance.

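### 80 patients per group does not give 80% power on the plan's own inputs: the standard formula needs 93 or 118 per group, and 80 gives about 75% or 64%

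*Protocol article*

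**What the plan says.** The Sample size estimate section of the protocol article supplies the inputs of a non-inferiority calculation for two proportions.

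- **Event rate:** "the anastomotic leakage rate in this trial is defined as 1.9" per cent, taken from an earlier laparoscopic gastrectomy trial. No separate rate is given for early oral feeding (EOF). The section cites open-gastrectomy trials in which "there were no significant differences between EOF and traditional oral feeding (DOF) with regard to the risk for anastomotic leakage".
- **Margin:** "a non-inferiority test with a non-inferiority margin of 5" per cent.
- **Error rates:** "α = 0.05, β = 0.20, and a power of 80" per cent. Whether alpha is one- or two-sided is not said.
- **Result:** "therefore, no less than 160 participants (80 participants in each group) will be required". A 20% allowance for drop-out and withdrawal then gives 200 (100 per group).

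The Statistical analysis section applies intention to treat to all analyses and closes with: "A blinded statistician will analyze all of the data using a two-sided *P* value < 0.05 to represent statistical significance".

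**The concern.** The section presents 80 per group as following from its inputs, yet 80 is smaller than the usual formula gives for them on either reading of alpha. The two sections also leave the sidedness unsettled. The sample size section is silent, and the only statement elsewhere is two-sided, which is the more demanding reading.

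This is the only sizing of the primary endpoint in a trial that its Treatment protocols section calls confirmatory. If feeding time truly makes no difference to leakage, the trial is more likely than advertised to end without showing non-inferiority. Readers who trust the 80% figure could then take an inconclusive result as evidence against early feeding.

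**Working it through.** **Inputs, all from the Sample size estimate section.** Leakage rate p = 0.019. It is taken in both arms, because one rate is defined for the trial and no difference is assumed. Margin d = 0.05, read as absolute percentage points. Power 80%, so z = 0.8416. Alpha 0.05: z = 1.6449 if one-sided, z = 1.9600 if two-sided (one-sided 0.025). Allocation is 1:1.

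**The plan's own figures.** The drop-out step reproduces: 160 / (1 − 0.20) = 200. The 80 per group does not.

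**Required size.** n per group = (z_alpha + z_beta)² × 2p(1 − p) / d², where 2 × 0.019 × 0.981 = 0.037278 and 0.037278 / 0.0025 = 14.911.

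- One-sided 0.05: 6.1826 × 14.911 = 92.19, so 93 per group (186 in total).
- Two-sided 0.05: 7.8489 × 14.911 = 117.04, so 118 per group (236 in total).

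Against these, 80 is short by 13/93 = 14% or 38/118 = 32%. With 20% loss, 93/0.8 = 116.25 gives 117 randomised per group, and 118/0.8 = 147.5 gives 148. The plan has 100.

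**Power actually delivered.** Power = Φ(d / √(2p(1 − p)/n) − z_alpha).

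- n = 80: standard error √(0.037278/80) = 0.02159 and 0.05/0.02159 = 2.316. Power is Φ(0.671) = 74.9% one-sided, or Φ(0.356) = 63.9% two-sided.
- n = 100: standard error 0.01931 and ratio 2.590. Power is Φ(0.945) = 82.8% one-sided, or Φ(0.630) = 73.6% two-sided.

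**Could another standard formula give 80?** Those tried all need more patients (per group, one-sided / two-sided 0.05):

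| Method | n per group |
|---|---|
| Unpooled normal approximation (above) | 93 / 118 |
| With continuity correction | 130 / 155 |
| Equivalence (two one-sided tests), each at 0.05 / 0.025 | 128 / 157 |
| Farrington–Manning score formula | 141 / 182 |
| Variance at 1.9% and 6.9% | 205 / 261 |
| Superiority formula, 1.9% vs 6.9% | 208 / 263 |

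**What would give about 80?** At one-sided 0.05, a target power of 75% gives 81. A common rate of 1.6% gives 78, and 1.65% gives 81. An EOF rate of 1.7% against 1.9% in the delayed oral feeding (DOF) arm also gives 81. None of these is stated.

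**Rare events.** At 80 per group the expected count is 80 × 0.019 = 1.52 leaks per arm, where the normal approximation is poor. Enumerating all binomial outcomes with 1.9% in both arms gives these exact powers (one-sided / two-sided 0.05):

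| n per group | Farrington–Manning score test | Wald test |
|---|---|---|
| 80 | 53.6% / 38.4% | 77.6% / 66.7% |
| 100 | 71.9% / 49.3% | 81.3% / 75.9% |

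The Newcombe interval gives the same power as the score test. The Wald test's higher power comes with inflated error. With true rates of 6.9% and 1.9%, its type I error at 80 per group is 9.2% against a nominal 5%, and 5.1% against a nominal 2.5%. The score test's is 3.8% and 1.6%. As an illustration, with 80 per group and the two-sided level, one leak in each arm already fails to show non-inferiority by the score test.

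**The case against.** Four points can be made for the plan.

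1. **The EOF rate need not be 1.9%.** The Background hypothesises similar or lower leakage with EOF, and at 1.7% the formula gives 81 per group. But the sample size section defines a single rate and no advantage. The rescue works only one-sided; at two-sided 0.05, 1.7% still needs 103. It shows how sensitive the number is, not that the stated number follows.

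2. **The trial randomises 100 per group and analyses by intention to treat.** Leakage is recorded daily in hospital, so losing 20% of primary outcomes may be pessimistic. With all 200 analysed, formula power is 82.8% at one-sided 0.05, which meets the claim. This stands, and the report should say so. It does not hold at two-sided 0.05 (73.6%), and it does not support the statement that 80 per group suffices.

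3. **The two-sided reading rests on one general sentence.** That sentence also governs the secondary outcomes, and a full protocol or SAP may specify otherwise. Fair, which is why both readings are shown. The figure of 80 fails under each.

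4. **The article does not name a score test.** Correct. The score-test figures are supplementary. The arithmetic finding rests on the plain formula, which is the more favourable calculation.

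The section's mention of clinical and statistical considerations, such as intolerance of enteral nutrition, does not help. An allowance of that kind can raise a required number but cannot bring it below the calculated one.

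**Conclusion.** The statement is wrong as written. On the inputs given, 80 per group yields about 75% power at one-sided 0.05 or 64% at two-sided 0.05. The chance of missing true non-inferiority is therefore about 25% or 36%, against the stated 20%. With a test that holds its type I error in this setting, power at 80 per group is about 54% or 38%. The recruited 100 per group reaches 80% only with one-sided 0.05, a Wald-type calculation and complete outcomes.

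This rests on equal true leakage of 1.9% in both arms, the only rate the document gives, and on reading the 5% margin as absolute percentage points.

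**What to change.** Keep the 200 patients and correct the statement.

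- State whether alpha is one-sided 0.05 or two-sided 0.05 (one-sided 0.025), and make the Sample size estimate and Statistical analysis sections agree.
- State the assumed EOF leakage rate (1.9% if equal rates are meant) and the formula used.
- Replace the claim that 80 per group gives 80% power with the power delivered: 74.9% (one-sided) or 63.9% (two-sided) at 80 per group, and 82.8% or 73.6% if all 100 per group are analysed.
- Give the exact score-test power alongside: 53.6% or 38.4% at 80 per group, and 71.9% or 49.3% at 100.

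The cost is a few restated and less favourable figures. No patients are added, and the endpoint and margin are unchanged. Enrolment was at 102 of 200 when the article was submitted.

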### Statistical analysis

The intention-to-treat principle will be applied in all analyses with an assumed drop-out rate. Normally distributed continuous variables will be described as the mean with corresponding SDs, and non-normally distributed or categorical variables will be described as medians with the corresponding range or percentages and frequencies. Normally or non-normally distributed continuous data will be compared by Student’s *t*-test or the Mann–Whitney U test, and the chi-square test and Fisher’s exact test will be used to compare categorical variables, as indicated. With the exception of the primary outcome, secondary outcomes, such as post-operative complications, time of first flatus and defecation, and post-operative length of stay, will also be compared. The potential risk factors for intolerance of EOF and post-operative complications will be identified using a multivariate analysis. A blinded statistician will analyze all of the data using a two-sided *P* value < 0.05 to represent statistical significance.

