### Treatment protocols

This is a confirmatory, single-site, non-inferiority RCT to assess the safety and feasibility of EOF after TLRG compared to DOF.

All eligible patients with gastric cancer will be randomly assigned in a 1:1 allocation ratio to the EOF or DOF group. Participants in both groups will undergo similar peri-operative procedures, with the exception of different oral feeding beginning times. All study data will be stored in an Excel 2007 file, which will be monitored by a nurse who is not involved in this study.

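### Intention-to-treat is the only analysis set for the non-inferiority claim, although the plan foresees intolerance of early feeding, which would dilute a true excess of leaks

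*Protocol article*

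**What the plan says.** All places are in the protocol article.

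- **Design** (Treatment protocols): "This is a confirmatory, single-site, non-inferiority RCT to assess the safety and feasibility of EOF after TLRG compared to DOF".
- **Primary endpoint** (Study endpoints): "The primary endpoint will be the percentage incidence of anastomotic leakage after TLRG".
- **Analysis set** (Statistical analysis): "The intention-to-treat principle will be applied in all analyses with an assumed drop-out rate". No per-protocol or as-treated analysis is mentioned anywhere.
- **Intolerance** (Sample size estimate): the evaluable number of 160 is introduced with "Considering both clinical and statistical considerations like intolerance of enteral nutritions". Intervention protocols makes later volumes depend on tolerance and describes when total parenteral nutrition is considered: intake below 60% of daily requirements on POD4, or suspected leakage. Statistical analysis plans a multivariate search for risk factors for intolerance of EOF.
- **Attrition** (Sample size estimate): "Allowing for a 20% drop-out and withdrawals before trial completion", the target is raised from 160 to 200.
- **Significance level**: the sample size uses α = 0.05 without stating sidedness. Statistical analysis says: "A blinded statistician will analyze all of the data using a two-sided *P* value < 0.05 to represent statistical significance".

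**The concern.** In a superiority trial, intention-to-treat is usually cautious because departures from treatment pull the arms together. In a non-inferiority trial the same pull favours the claim. By the article's own account the arms differ only in when oral feeding starts, so an EOF patient who is not fed early has, for this comparison, been treated much like a DOF patient.

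If early feeding did raise the leak rate, such patients would hide part of the rise. A per-protocol analysis beside intention-to-treat is the usual check. This is not a detail left to an unseen analysis plan: the article assigns intention-to-treat to every analysis.

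The phrase about an assumed drop-out rate adds to the difficulty. An assumed drop-out rate is an input to the sample size. It does not say who is analysed or how a patient with unknown leak status is counted.

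**Working it through.** **Inputs from the article.** DOF leakage 1.9%; margin 5%, read as 5 percentage points; 80 evaluable and 100 recruited per arm; power 80%; α = 0.05. Because sidedness is unclear, both one-sided 5% and one-sided 2.5% are shown.

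**Inputs assumed.** A fraction f of EOF patients is not fed early and carries the DOF risk; f = 10%, 20% and 30% are tried. The true rate in those fed early is 1.9% + 5.0% = 6.9%, exactly at the margin.

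**The plan's own figures.** The drop-out step reproduces: 80 / (1 − 0.20) = 100 per arm. The 80 does not. The simplest formula, n = (z₁₋α + z₀.₈₀)² × 2 × 0.019 × 0.981 / 0.05², gives:
- one-sided 5%: 6.183 × 0.037278 / 0.0025 = 92.2, so 93 per arm
- one-sided 2.5%: 7.849 × 0.037278 / 0.0025 = 117.04, so 118 per arm

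That is a separate matter and is not needed below.

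**Dilution.** The EOF rate under intention-to-treat is (1 − f) × 6.9% + f × 1.9%, so the observed excess is (1 − f) × 5 points. The probability of declaring non-inferiority was found by enumerating all pairs of leak counts with 100 per arm, using the restricted-maximum-likelihood score test against a 5-point difference.

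| f (assumed) | EOF rate | Excess, points | False non-inferiority, one-sided 5% | One-sided 2.5% |
|---|---|---|---|---|
| 0 | 6.9% | 5.0 | 4.6% | 2.0% |
| 10% | 6.4% | 4.5 | 6.4% | 2.8% |
| 20% | 5.9% | 4.0 | 9.0% | 4.1% |
| 30% | 5.4% | 3.5 | 12.3% | 5.8% |

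**Cross-check by normal approximation at f = 20%.** SE = √(0.059 × 0.941/100 + 0.019 × 0.981/100) = 0.0272. The probability is Φ((0.05 − 0.04)/0.0272 − z₁₋α) = Φ(0.367 − 1.645) = 10.1%, or Φ(0.367 − 1.960) = 5.6%. With f = 0 these are 5.0% and 2.5%. Either method shows the error about doubling at 20%.

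**Unknown leak status.** The article gives no handling rule. Taking 20% unknown as a ceiling, with a true excess of 5 points and the normal approximation from 100 randomised per arm:

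| Handling | Expected excess, points | False non-inferiority, 5% / 2.5% |
|---|---|---|
| Both arms, counted as no leak | 4.0 | 10.4% / 5.8% |
| EOF only, counted as no leak | 3.6 | 13.0% / 7.5% |
| Complete cases, missing at random (80 per arm) | 5.0 | 5.0% / 2.5% |
| DOF only, counted as no leak | 5.4 | 3.8% / 1.8% |
| Both arms, counted as leak | 4.0 | 7.0% / 3.6% |

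In the last row, power at equal true rates falls from 83% / 74% to 22% / 14%. The direction therefore depends on the rule and on which arm loses patients.

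**The case against.** **The dilution may be small, and is partly the question asked.** The EOF schedule is flexible, so a patient who takes little may still be on the assigned strategy. Intolerance is judged on POD4, after early feeding has been offered on POD1–3, so these patients do not simply carry the DOF risk. For a policy of offering early feeding, a diluted excess of 4 points is a true result below the margin; the error rates above refer to the effect in those actually fed early. All this stands. It makes the table an upper illustration and is a reason to keep intention-to-treat. It does not justify having no second analysis in a trial whose question is whether early feeding itself is safe.

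**Stronger readings the article does not support:**
- *The 20% is a non-adherence rate.* It is drop-out and withdrawal before trial completion, which includes visits 4 and 12 weeks after discharge.
- *Lost outcomes push the result towards non-inferiority.* The second table shows they may do so, have no effect, or push the other way. Leakage is recorded daily on POD1–6, so actual loss may be well below 20%.
- *Planning 160 out of 200 contradicts intention-to-treat.* Raising recruitment for attrition is ordinary practice, and the article does not say intolerant patients leave the analysis.
- *A single leak decides the verdict because of the analysis set.* With 100 per arm, 2 v 2 leaks gives a score p of 0.029 and 3 v 2 gives 0.068, but a Wald test of 3 v 2 gives 0.035. That fragility comes from sparse events and the test chosen, and would be present in a per-protocol set too.

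**Conclusion.** The point holds in a limited form. The article fixes intention-to-treat for every analysis of a confirmatory non-inferiority trial while foreseeing departures from early feeding. At an assumed 20% of EOF patients with the DOF risk, the false non-inferiority rate is about double that under full adherence, at either one-sided level (4.6% to 9.0%, or 2.0% to 4.1%).

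This rests on an assumed non-adherence rate, a true excess exactly at the margin, complete loss of the early-feeding risk in non-adherers, and 100 analysed per arm. The third assumption is generous, so the real inflation is probably smaller. No direction of bias can be claimed for lost outcomes. The change should be made, but intention-to-treat need not be abandoned.

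**What to change.** In Statistical analysis:

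1. Keep intention-to-treat as the main analysis: all randomised patients who have the operation, in their assigned arm, with leak status ascertained whatever happens to feeding.
2. Add a per-protocol analysis of the primary endpoint, defined as feeding started as assigned. It must never exclude a patient because feeding was withheld or stopped for suspected or confirmed leakage; that would remove events and itself favour non-inferiority. The definition needs one DOF start window: Intervention protocols gives both POD4 and POD4 to POD6, and these must be reconciled.
3. Claim non-inferiority only if the per-protocol conclusion is consistent with intention-to-treat. A strict rule that both must pass is more debatable, because the per-protocol comparison is smaller and no longer fully randomised.
4. Delete the closing phrase about an assumed drop-out rate.
5. Add a sensitivity analysis, such as a tipping-point analysis, for any unknown leak status, without presuming its direction.

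**Cost.** No new patients are needed; the work is a wording change, the per-protocol analysis and the sensitivity analysis. The chance of success falls somewhat. If the per-protocol set were 80 per arm with 1.9% in both arms, its power by normal approximation is about 75% at one-sided 5% or 64% at 2.5%, against 83% or 74% with 100 per arm. The exact score calculation gives lower values: 54% or 38% with 80 per arm, against 72% or 49% with 100. With 102 of 200 recruited when the article was submitted, the change should be settled before unblinded data are seen.

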### Peri-operative procedures

Before surgery, gastroscopies, endoscopic biopsies, and computed tomography scans will be performed to confirm the tumor size and location, and patients with organic metastases will be excluded based on assessment by two experienced pathologists. The ERAS guidelines will be followed and all participants will receive pre-operative education, pre-emptive and multimodal analgesia, early ambulation, and laparoscopic radical gastrectomy as part of the peri-operative treatment.

Laparoscopic radical gastrectomies will be performed by the same experienced surgical teams, who have carried out this procedure with an annual caseload of approximately 100 gastric cancer patients. The main anastomosis will be completed laparoscopically, and the abdominal incision will be < 10 cm. After the gastrectomy, Roux-en-Y, Billroth II, or Billroth I reconstruction will be performed in distal gastrectomies and Roux-en-Y esophagojejunostomy in total gastrectomies. Considering the possibility of anastomotic leakage, a peri-anastomotic drain will be placed near the anastomosis after surgery. In most cases, the nasogastric tube will be removed on POD1 and use of a nasojejunal tube will be avoided.

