### Data collection and schedule

Once informed consent is signed, baseline data, such as age, gender, body mass index (BMI), and complications, will be collected by a clinical research assistant. The laboratory data (total serum protein, serum albumin, and blood glucose) will also be tested pre-operatively and during hospitalization to monitor the patients’ nutritional status. A specified operator will record the details of surgical procedures, such as the operative approach, the location of the tumor, lymph node metastasis, and pathologic TNM stage.

From POD1–6, clinical observation data (anastomotic leakage, the time of first flatus and defecation, NRS pain score, post-operative hospital stay, and complications) will also be recorded daily to evaluate the post-operative recovery by an investigator. The clinicians will be responsible for patient care and will not be involved in data collection.

The contact information and address of patients will be confirmed before hospital discharge. Two follow-up visits will be carried out in the outpatient clinic or via telephone 4 and 12 weeks after hospital discharge, focusing on tolerance of the diet and any discomfort. The details of the schedule are shown in Fig. 2.

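### The secondary outcomes are compared only with unadjusted tests; pre-specified adjustment for tumour location would give a modest, nearly free gain in precision

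*Protocol article*

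**What the plan says.** **Tests.** In the Statistical analysis section, "Normally or non-normally distributed continuous data will be compared by" Student's t-test or the Mann–Whitney U test. Chi-square and Fisher's exact tests "will be used to compare categorical variables, as indicated". None of these takes a covariate. The same paragraph then says that "secondary outcomes, such as post-operative complications, time of first flatus and defecation, and post-operative length of stay, will also be compared". Hospitalisation cost is not in that sentence but is listed as a secondary endpoint under Study endpoints.

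**The one multivariable analysis.** "The potential risk factors for intolerance of EOF and post-operative complications will be identified using a multivariate analysis". Its stated aim is to find risk factors. It is not described as an adjusted comparison of early (EOF) with delayed (DOF) oral feeding, and it does not cover stay, cost or bowel recovery.

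**Mix of operations.** Under Peri-operative procedures, "Roux-en-Y, Billroth II, or Billroth I reconstruction will be performed in distal gastrectomies and Roux-en-Y esophagojejunostomy in total gastrectomies". The shares are not given.

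**Allocation.** The Randomization procedure section describes a 1:1 ratio and mentions no stratification factor.

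**Available covariate.** Before surgery, gastroscopy, biopsy and "computed tomography scans will be performed to confirm the tumor size and location". Data collection and schedule lists "the operative approach, the location of the tumor, lymph node metastasis, and pathologic TNM stage" among the recorded details.

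**The concern.** Total and distal gastrectomy are different operations, and extent of resection plausibly predicts stay, cost, return of bowel function and complications. An unadjusted comparison leaves that between-patient variation in the error term. With no stratification described, the two arms can also differ by chance in their share of total gastrectomies, and an unadjusted estimate does not correct for this.

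The secondary outcomes matter in this trial. Non-inferiority on leakage can show only that early feeding is not unacceptably worse. The Background hypothesises fewer complications and faster recovery, and the Discussion says that benefit will be assessed, so any claim of benefit rests on these comparisons. Tumour location is the pre-operative marker of extent. It is known before surgery, so feeding time cannot alter it, and it is already recorded.

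**Working it through.** The document states no figure for precision or power on any secondary outcome, so there is nothing of its own to reproduce on this point. The check is a range under stated assumptions.

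**Inputs from the document**
- 100 patients per arm (Sample size estimate); the inflation 160/(1 − 0.20) = 200 is consistent.
- Leakage rate 1.9% (same section).

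**Assumed inputs (not in the document)**
- q, the share of patients in the location group that leads to total gastrectomy: 0.2 to 0.5.
- D, the difference in mean outcome between location groups, in within-group SDs: 0.25 to 1.0.

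**1. Variance explained by a binary covariate.** R² = q(1 − q)D² / [1 + q(1 − q)D²].
- Low end, q = 0.2, D = 0.25: 0.16 × 0.0625 = 0.01; R² = 0.01/1.01 ≈ 0.01.
- Middle, q = 0.3, D = 0.5: 0.21 × 0.25 = 0.0525; R² = 0.0525/1.0525 ≈ 0.05.
- High end, q = 0.5, D = 1.0: 0.25 × 1 = 0.25; R² = 0.25/1.25 = 0.20.

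**2. Gain from adjustment.** The standard error is multiplied by √(1 − R²), and N patients act like N/(1 − R²). The last column is power for a continuous outcome with an assumed effect of 0.4 SD, 100 per arm, two-sided 5%; without adjustment it is 80.7%.

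| R² | SE ratio | SE reduction | 200 patients act like | Power |
|---|---|---|---|---|
| 0.01 | 0.995 | 0.5% | 202 | – |
| 0.02 | 0.990 | 1.0% | 204 | 81.5% |
| 0.05 | 0.975 | 2.5% | 211 | 82.7% |
| 0.10 | 0.949 | 5.1% | 222 | 84.6% |
| 0.20 | 0.894 | 10.6% | 250 | 88.5% |

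The formula ignores the small cost of estimating one extra coefficient, so at the low end the net gain is close to nil.

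**3. Chance imbalance.** SD of the between-arm difference in share = √[2q(1 − q)/n], with n = 100.
- q = 0.2: √(0.32/100) = 0.057; 95% range ±1.96 × 0.057 ≈ ±11 percentage points.
- q = 0.5: √(0.50/100) = 0.071; 95% range about ±14 percentage points.
- The probability of a difference above 10 points is about 8% (q = 0.2) to 16% (q = 0.5).

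At D = 0.5, an imbalance at the edge of the 95% range shifts the estimate by 0.5 × 0.111 = 0.055 SD to 0.5 × 0.139 ≈ 0.07 SD. The standard error of a mean difference with 100 per arm is √(2/100) = 0.141 SD, so even this extreme shift is about 0.055/0.141 = 0.4 to 0.07/0.141 = 0.5 of one standard error.

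**4. Primary endpoint.** Expected leaks: 200 × 0.019 = 3.8. That is too few to support a covariate.

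**The case against.** The strongest case against is that nothing here is wrong. Two-sample tests in a 1:1 randomised trial keep their type I error, and they match the allocation described: no stratification factor is stated and then ignored. Covariates for secondary outcomes are often settled in an analysis plan, and that plan is not shown. All of this stands. It makes the point an optional improvement, and it means that the analysis plan may already contain it. The point survives because the article does not leave the method open: it names the tests, and none of them adjusts.

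Four stronger readings might be inferred, and the document supports none of them.

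- **That the comparisons are biased.** Imbalance arising by chance after randomisation is random error, and the unadjusted interval already allows for it. Adjustment corrects the estimate for the imbalance observed; it does not remove a bias.
- **That no multivariable analysis is planned.** One is, and it covers complications, although its aim is risk factors.
- **That planned extent of resection is on file.** No section says so. Tumour location is recorded, but in a list of operative details, so it needs confirming that the pre-operative value is captured. The article also does not say whether randomisation precedes surgery, so the operation performed is a less safe covariate than pre-operative location.
- **That the gain is substantial.** It rests on assumed inputs and may be negligible.

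Two technical objections also stand in part. Replacing a rank test by regression on means changes the quantity estimated, which matters for skewed stay and cost; a stratified rank test avoids this. For complications, an adjusted odds ratio is not comparable with the unadjusted one because odds ratios are non-collapsible; a Mantel-Haenszel risk difference avoids that.

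**Conclusion.** The point holds as a low-priority efficiency improvement. The named comparisons of secondary outcomes are unadjusted, the operations are mixed, no stratification is described, and a suitable pre-operative covariate is recorded. The planned tests are valid, and nothing shows that a trial conclusion would change. The reduction in standard error is about 0.5% to 11% if 20% to 50% of patients fall in the location group leading to total gastrectomy and the outcome differs by 0.25 to 1.0 SD between location groups. The document gives neither quantity, so the range is illustrative. The benefit applies mainly to stay, cost and bowel recovery, less clearly to complications, and not to the primary endpoint.

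**What to change.** Before unblinding, add to the analysis plan:

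- The EOF versus DOF comparison of length of stay, hospitalisation cost and time to first flatus and defecation is adjusted for tumour location, using the pre-operative value and categories fixed in advance.
- The method is regression on a suitable scale or, for skewed outcomes, a rank test stratified by location. The choice for each outcome is fixed in advance.
- The t, Mann–Whitney, chi-square and Fisher tests already named are kept as sensitivity analyses.
- Complications may be compared with a Mantel-Haenszel risk difference stratified by location if there are enough events.
- The primary leakage comparison stays unadjusted.

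The cost is a few sentences of analysis wording, a check that location is held as a pre-operative value, slightly more analysis work, and a modelling assumption where regression is used. No change to recruitment or allocation is needed. With 102 of 200 patients already recruited (Trial status), stratified allocation could no longer cover the whole trial, whereas adjustment in the analysis can.
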